## Abstract

**Background:**

The effects of climate change on mental health are becoming widely recognized. Mental health can be impacted through direct and indirect exposure to natural hazards, as well as through the overarching awareness of climate change and the resultant environmental decline—the latter is termed eco-anxiety. Exposure to natural hazards also increases eco-anxiety, further compounding mental health impacts. Young people are especially vulnerable to the mental health impacts of climate change and have higher rates of eco-anxiety than other age groups. Those in rural areas are also more likely to be impacted by natural hazards, further underscoring the need to support this population. To date, there remains scant evidence regarding how to support young people with eco-anxiety, and few interventions, especially for children, have been evaluated. There is a need for further research to inform treatment for young people for climate change–related distress.

**Objective:**

This study pilots a novel group-based mental health and resilience intervention in relation to eco-anxiety. Specifically, this project aims to explore the acceptability, feasibility, and clinical utility of a group-based eco-anxiety intervention.

**Methods:**

The project is an exploratory pilot assessing the acceptability, feasibility, and clinical utility of a group-based intervention using a pre-post design with a single group. A minimum sample of 12 children aged 10-14 years located in a rural area and with exposure to at least one natural hazard will be enrolled in this study. In order to assess clinical utility, changes from preintervention to postintervention in distress, resilience, and climate emotions will be assessed. To do so, children will complete measures of psychological distress (subjective units of distress, Depression Anxiety Stress Scale-21–youth version), climate emotions, and resilience (Resilience Scale for Children-10) before and after the intervention. Acceptability will be assessed post intervention through a series of Likert scale and open-ended questions. Feasibility will be assessed through enrollment and the proportion of participants completing the full intervention. Eligible children will take part in a novel 5-module group-based intervention designed to build resilience, promote nature connectedness, build social support, and foster meaning-focused coping.

**Results:**

This study has received ethics board approval by the University of New England’s Human Research Ethics Committee (HE23-080). This study will be conducted from late 2024 to 2025. As of March 2025, 28 children have been enrolled in the study.

**Conclusions:**

Rural children and young people are an especially vulnerable population for the mental health impacts of climate change. To date, the evidence base for interventions for treating eco-anxiety remains sparse, especially for young people and children who typically have higher rates of eco-anxiety than older age groups. This study will provide preliminary evidence of a group-based treatment for children and adolescents experiencing eco-anxiety that can inform practitioners.

**Trial Registration:**

Australia and New Zealand Clinical Trials Registry ACTRN12624001287527; https://www.anzctr.org.au/Trial/Registration/TrialReview.aspx?id=388545

**International Registered Report Identifier (IRRID):**

PRR1-10.2196/69005

## Introduction

### Climate Change and Mental Health

Climate change is an ecological crisis that poses a significant threat to human health [1]. It has been widely reported that climate change can negatively impact mental health [2,3], both through direct and indirect exposure to natural hazards, as well as through the overarching awareness of climate change and the associated environmental decline, known as eco-anxiety [4]. The detrimental impacts of exposure to natural hazards such as bushfires and drought on mental health and well-being have been widely reported and can be enduring [5-7]. An emerging body of research has also routinely highlighted the deleterious impact of eco-anxiety on a range of mental health outcomes [8,9]. As climate change continues to accelerate the intensity, frequency, and severity of climate-related natural hazards [10], there is an increased likelihood of exposure and repeated exposures to these events. Direct exposure to natural hazards also increases climate change distress and concern [11], compounding exposure-related distress and leaving exposed individuals especially vulnerable to poor mental health outcomes.

### Climate Change and Young People

Although much of the existing literature has explored the mental health outcomes of adults, children and young people are considered to be a priority at-risk group in relation to climate change [12,13]. Children are likely to be the most affected by climate change [14,15] and from early and developmentally significant life stages [16] while having contributed minimally to the climate crisis. Young people around the world report high levels of climate change concern [17], with higher levels of eco-anxiety observed in young people than in older age groups [18-21]. These high rates of eco-anxiety are also related to distress and poor mental health in children [22,23].

Young people are also especially vulnerable to direct and indirect exposure to natural hazards [24], in part due to exposure to parental stress [25,26] and erosion of normal support systems [27] at an age where coping skills are still emerging [28]. Recent evidence highlights high levels of depression, stress, anxiety, substance misuse, adjustment disorder symptoms, and low resilience in young people following the Black Summer 2019-2020 bushfires in Australia, especially for those who were directly exposed [11]. Children and young people residing in rural areas are further at increased susceptibility to poor mental health in relation to climate change due to (1) already higher rates of psychological distress compared with their metropolitan counterparts [29], (2) more likely exposure to adverse climate change–related hazard events, and (3) limited mental health service access in rural areas [30]. Despite the body of evidence pointing to the impacts of climate change on mental health, evidence to guide practice remains scant, with few interventions for eco-anxiety currently evaluated [3,31].

### Climate Change and Resilience

Psychological resilience is a key protective factor for mental health and is understood as a process of adaptation to a stressor [32]. It has been argued that building resilience may be a key way to protect against impacts of climate change on mental health [33-35]. Climate change resilience—the ability to prepare for, adapt, and respond to climate-related hazards such as extreme weather events [36]—has most commonly focused on physical resilience, with less emphasis to date on how to build or foster psychological climate-resilience (ie, the ability to psychologically adapt to climate-related stressors).

Although psychological resilience has been widely studied, how to best build resilience and how resilience intersects with broader social factors and challenges such as climate change remains less well established [32]. Concomitantly, research examining how to build psychological climate-resilience remains in the nascent stages. This study thus crucially builds the literature base around developing psychological climate resilience in children in order to protect mental health.

### Interventions

To date, evidence for interventions to support climate change–related distress remain scant, and interventions proposed to date lack empirical assessment. Suggestions from the limited literature point to fostering hope and optimism [37] and empowering young people to feel a sense of efficacy to support coping—such as through taking climate action—as potentially beneficial [22,24]. Meaning-focused coping in relation to climate change has been shown to predict better mental health outcomes in young Swedes [38], suggesting the potential value of fostering this specific coping style. However, allowing children to explore and express negative emotional states is also critical [39]. Additionally, the use of ecotherapy, enhancing connection with nature [31,40], and mindfulness, alongside psychoeducation [33] have also been proposed. Group-based approaches may also be well placed to treat eco-anxiety, allowing for social support [31]. Given that the mental health care sector will struggle to cope with the impacts of climate change [33,41,42], group-based approaches may also be more feasible as a treatment modality. However, little is known regarding the effectiveness of any eco-anxiety–informed interventions, with minimal evaluation of any interventions currently undertaken [31].

### Goal of This Study

This study pilots a novel group-based mental health and resilience intervention in relation to eco-anxiety for rurally located children who have been impacted by natural hazards. Specifically, the objective of this project is to explore the acceptability, feasibility, and clinical utility of a group-based eco-anxiety intervention.

## Methods

### Design

This project is an exploratory trial to assess the acceptability, feasibility, and clinical utility of a group-based intervention using a pre-post design with a single group (trial registration ACTRN12624001287527). This protocol is presented in line with SPIRIT (Standard Protocol Items: Recommendations for Interventional Trials) reporting guidelines [43].

### Participants

#### Sample Size

Being an intervention pilot precludes definitive sample size calculation [44]. However, it has been argued that, for clinical intervention pilots, a minimum of 10 samples in the intervention group is required [45]. In order to allow for up to 20% attrition and ensure sufficient data for preliminary efficacy testing, a minimum sample of 12 is anticipated, which is sufficient to provide acceptability and feasibility data and preliminary data regarding clinical utility [44].

#### Setting

This pilot study is conducted in a rural region of northern New South Wales, Australia, with a population of approximately 80,000 people. This area is largely agricultural-dependent. The study is conducted in a community setting.

#### Eligibility

##### Inclusion Criteria

Persons aged 10-14 years, of any gender, living in a rural area (defined as areas with a Modified Monash Model 3 or higher, representing large rural towns through to remote communities) with self-reported exposure to one or more natural hazards (eg, fire, flood, tornado, drought) are included in this study. Given that the impacts of hazard exposure can be sustained well past the initial exposure [5,6], there are no time limits on exposure to the hazards. There are no restrictions on participants currently or previously having accessed other mental health interventions.

##### Exclusion Criteria

Persons outside of the age range, not residing in a rural area, or without exposure to a natural hazard are excluded from this study. Individuals who fail comprehension checks as ascertained by clinicians during provision of child assent or who have acute suicidal risk or a cognitive impairment/disability as reported by parents are also excluded.

#### Recruitment

Recruitment will occur through rural mental health and health care services, as well as through community groups and organizations and school-based well-being officers and psychologists. In particular, recruitment includes placing flyers and sharing project information with local Headspace and health centers, the University psychology clinic (which receives referrals for young people), and local youth organizations. Additionally, the project was presented to school psychologists and well-being officers to refer children to the project. Recruitment commenced in late 2024, with 28 children currently enrolled in the study.

### Intervention

#### Development

Taking the best available evidence for treating eco-anxiety in young people and extensive consumer consultation and co-design, a group-based eco-anxiety intervention was developed. An expert and consumer advisory group consisting of a range of professionals, including teachers, psychologists, school well-being officers, environmental psychology researchers, and young end users provided co-design input into the development and refinement of the intervention manuals [46,47] and workbooks [48,49]. The Bee Well intervention has been developed both for teenagers (15-18 years) and children/adolescents (10-14 years); this protocol relates only to the child/adolescent version of the intervention.

#### Intervention Overview

The Bee Well intervention is informed by the resilience-building empirical evidence, alongside emerging evidence surrounding coping with climate change [37,38], which also points to the value of ecotherapy, nature connectedness, and nature immersion [40]. The intervention is designed to be run in a group setting in order to normalize climate change–related emotions and foster social support [31]. The intervention takes place predominantly outdoors to enable nature exposure and connection and consists of guided discussion and activities that focus on providing psychoeducation on emotional awareness and climate emotions, developing adaptive coping strategies for coping with climate change distress and hazards, and building resilience (see Table 1). The intervention also includes a nature restoration–based activity, occurring alongside discussions around meaning-making and coping, in order to foster efficacy and engage in shared action. Group members have their own individual workbooks and complete a range of individual and group activities, in addition to the nature restoration task. The intervention consists of 5 modules, with each module lasting approximately 60 minutes and will be co-delivered by a team of provisional and clinical psychologists with an interest in child and adolescent mental health, rural health, and/or eco-anxiety.

**Table 1 table1:** Intervention modules.

Module	Description	Purpose
Module 1: Finding Common Ground	In this module, individuals explore and share their own eco-emotions, including grief, worry, and hope, through 2 interactive group activities (exploring eco-emotions and exploring mixed feelings).	Psychoeducation regarding emotions; build emotional awareness, recognition of shared experiences, and enable group processing
Module 2: Taking Action Together	In this module, the group commences a shared nature restoration activity—flora-based or fauna-based—such as building bee hives. While engaging in the activity, the group also undertakes guided discussions regarding “taking action” and exploring their own relationships with nature.	Taking action together through engaging in nature restoration as a form of coping and building group-efficacy and a means to support meaning making and fostering peer connection
Module 3: Coping	In this module, the group is introduced to coping skills through activities and group discussions. Group members undertake a mindfulness nature meditation/journaling task as a means of connecting with nature and rewilding.	Build adaptive coping skills, including promoting nature connectedness as a means of coping, and fostering resilience
Module 4: Cultivating Resilience	In this module, the group completes the nature restoration activity. Further discussions focus on fostering resilience and developing individual coping and resilience plans.	Build sense of community, group-efficacy, and self-efficacy; build resilience
Module 5: Bringing It Together	In this module, the group reflects on the nature restoration activity and discusses how this project will restore nature into the future. This module also includes a final reflection on the learnings and outlines avenues for ongoing or future support.	Reflection on the intervention and learnings

The Bee Well intervention resources can be found in the publicly available manual and workbook [47,49]. The intervention delivery is provided by trained psychologists who are able to manage referral or escalation, as needed, should any distress arise from or during participation. Information on referral sources is also provided to parents as part of the information sheet.

### Outcomes

Data will be collected before and after the intervention. The primary assessed outcomes will include changes in the psychological symptoms, resilience, and subjective ratings of distress, with secondary outcomes examining change in climate emotions, from preintervention to postintervention. Acceptability will also be assessed post intervention. Data will be collected by trained independent data collectors.

#### Psychological Distress

Psychological distress will be assessed using the Depression Anxiety Stress Scale (DASS)-youth version [50], which is a child and adolescent adaptation of the well-validated and widely used DASS-21 [51]. The measure consists of 21 items, with 7 items assessing each of the 3 conditions: depression, anxiety, and stress. Participants are asked to specify the frequency on a 4-point Likert scale (never to almost always), with which they have experienced symptoms. The DASS-youth version has replicated the original factor structure of the DASS-21 and has been validated for use in children aged 7-18 years [50].

#### Resilience

Resilience will be assessed using the Resilience Scale for Children [52]. This 10-item measure assesses individual resilience capacity in relation to 5 domains: sense of purpose and meaning, authenticity, equanimity, self-reliance, and perseverance. Respondents are asked to respond to a series of statements (eg, I think I’m okay just the way I am right now; when I get upset, I know how to calm down), indicating how well each statement described them. Items are scored on a 4-point Likert scale (1-4) from “not at all like me” to “a lot like me,” with higher scores suggesting greater resilience. The Resilience Scale for Children is validated for use in children as young as 7 years [52].

#### Climate Change Emotions

Two items will be used to assess distress in relation to climate change. The first asks participants to respond to the question “are you worried about climate change?” on a 5-point Likert scale ranging from “not worried” to “extremely worried.” The second item provides respondents with a list of 9 emotions (sad, helpless, worried, scared, hopeful, mad, hurt, powerless, and not bothered) and asks them to indicate if they feel each of these in relation to climate change (yes/no/prefer not to say). These items are adapted from Hickman et al [17]. The original items were designed for adolescents aged 16 years and older. Therefore, the wording of these items has been slightly modified to better suit the younger age range by psychologists with experience working with children and adolescents.

#### Subjective Units of Distress

This is a widely used short tool that asks respondent to rate how they are currently feeling. Children are presented with a feelings thermometer and asked to indicate how they are feeling from 0 to 10 (with 0 representing feeling happy/fulfilled/relaxed and 10 representing highest anxiety/distress ever felt).

#### Acceptability

Acceptability will be assessed through a series of 5-point Likert scale questions that are specifically designed for this intervention and based on our previous work [53]. Items such as “The workshop helped me feel better” are rated from strongly agree to strongly disagree. A series of open-ended questions regarding preferred and dispreferred components of the intervention, such as “what do you like about the workshop?” and “what did you not like?” are also asked to assess acceptability. Open-ended questions are also able to provide information on any unintended outcomes.

### Data Management

Hard copy data are collected and reviewed for any missing or inaccurate data. Data are then entered by a trained researcher. Data entry will be verified by a second researcher and all values inspected to ensure data quality. Hard copy data are securely stored in a locked filing cabinet. Unique identifier codes are stored separately to the data and accessible only to the project leads. Electronic data are securely stored on password-protected University cloud system. All data management and analyses are undertaken by the research team and are independent of the funding body. Adverse events will be identified by the research team through review of pre-post data upon collection. The research team will have access to the final deidentified dataset. Due to the small and short-term pilot nature of the study, no independent auditing systems are in place.

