### Ethical Considerations

This study has been approved by the University of New England’s Human Research Ethics Committee (HE23-080). Parental consent will be provided prior to children taking part in the study. The confidentiality and the nature of the study will be explained to the participants, and their assent will also be obtained prior to the commencement of the intervention. Study data will be deidentified, with participants assigned a unique code for linking their preintervention and postintervention data. Any potentially identifiable information provided in the open-ended responses will also be removed from any published materials to ensure privacy. Parents and children will be made aware that they are able to withdraw at any time without providing a reason and without consequence, and adherence will be recorded as the number of modules completed. Protocol amendments will be reported to the ethics committee and the trial registry. Catering during the intervention modules is provided, but no other compensation is provided to the participants.

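### The one stated adverse event route, review of pre-post data, sees harm during modules only in retrospect and misses any child without post data

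*Protocol article*

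**What the plan says.** Under Data Management the protocol article gives one rule for harms: "Adverse events will be identified by the research team through review of pre-post data upon collection". Under Outcomes it fixes the collection times: "Data will be collected before and after the intervention". What lies between those times is described in Intervention Overview: "The intervention consists of 5 modules, with each module lasting approximately 60 minutes".

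Three other places bear on harm:

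- Intervention Overview says delivery is by "trained psychologists who are able to manage referral or escalation, as needed, should any distress arise from or during participation". It does not say that a referral or escalation is recorded as an adverse event.
- The Acceptability section adds that "Open-ended questions are also able to provide information on any unintended outcomes". Outcomes places these items after the intervention: "Acceptability will also be assessed post intervention".
- Ethical Considerations tells families that "they are able to withdraw at any time without providing a reason", with adherence recorded as the number of modules completed. It does not say whether a child who stops is asked for post data.

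Data Management also says that the study has no independent audit.

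**The concern.** The plan foresees distress during participation and has psychologists at hand to deal with it, yet its adverse event rule looks only at the two questionnaire times. Module 1 asks hazard-exposed children aged 10-14 to share emotions such as grief and worry. A child could be escalated in that session and, on the rule as written, not appear in the harms count.

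Leavers are the second gap. The rule compares pre with post, so a child with only a pre form offers nothing to compare. If distress is a reason for leaving, the children most likely to have been harmed are the least likely to be counted. A pilot meant to inform practitioners and later trials could then report no adverse events when the count had missed the children who matter most for that statement.

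**Working it through.** **1. What each source can show about harm during a module**

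| Source | When | Reach |
|---|---|---|
| Subjective units of distress | Pre and post | Asks about current feeling, so a post score does not show distress in an earlier module that has since settled |
| DASS-youth | Pre and post | Frequency of symptoms; the article gives no recall period, so its reach back into the modules cannot be judged |
| Open-ended items | Post | Can reveal harm in a module, if the child volunteers it |
| Psychologists' referral or escalation | During modules | Direct observation, but no stated link to the adverse event count |

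For completers, capture is retrospective and partial. The one source that sees events as they happen is the one not tied to the rule.

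**2. The plan's own attrition figure**

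Sample Size starts from 10 and sets a minimum of 12: "In order to allow for up to 20% attrition". The stated 12 is 10 × 1.2 = 12; dividing instead gives 10 / 0.8 = 12.5, or 13. The difference has no bearing on this point. Note that 20% is a ceiling, not an expected rate.

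**3. How many may leave with the feasibility criterion still met**

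Planned Data Analysis sets 80% completion.

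- n = 28 (enrolled by March 2025): 0.8 × 28 = 22.4, so at least 23 must complete and up to 5 may leave (23/28 = 82.1%).
- n = 12 (minimum): 0.8 × 12 = 9.6, so at least 10 must complete and up to 2 may leave (10/12 = 83.3%).

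**4. What could stay unseen**

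Assume that the leavers give no post data. If no event is seen in completers, and completers truly had none, the proportion of enrolled children harmed lies between 0 and m/n:

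- n = 28: 5/28 = 17.9%
- n = 12: 2/12 = 16.7%

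The share of all events falling outside the stated route is m·RR / (m·RR + n − m), where RR is the risk in leavers relative to completers. The documents give no RR, so a range is shown:

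| RR (assumed) | n = 28, m = 5 | n = 12, m = 2 |
|---|---|---|
| 1 | 5/28 = 18% | 2/12 = 17% |
| 2 | 10/33 = 30% | 4/14 = 29% |
| 3 | 15/38 = 39% | 6/16 = 38% |
| 5 | 25/48 = 52% | 10/20 = 50% |

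**5. A figure that does not measure the problem**

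The one-sided 95% upper bound for zero events is 1 − 0.05^(1/n): 12.2% for n = 23 and 10.1% for n = 28. The gap of 2.1 percentage points reflects lost sample size only. It carries over to all enrolled children only if leavers resemble completers, which is the assumption in doubt.

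**The case against.** The rule names one route and excludes no other. This is a journal article, and session notes, escalation records or reporting to the ethics committee may be set out in a fuller protocol or in the intervention manual. Trained psychologists are present, parents receive referral information, and the open-ended items invite children to say what they did not like.

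Much of this stands, and it limits the point. A reader might infer that harm during modules cannot be counted at all. The documents do not support that, because a completer can report it afterwards. A reader might also infer that a child who leaves gives no post form. The article does not say so: stopping the modules and lacking post data are different things, and only the second puts a child outside the rule. Last observation carried forward would give a leaver with baseline data only a change of exactly 0, but that governs the outcome analysis, not how adverse events are identified.

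The objection does not remove the point. The article does not leave adverse event identification to another document; it states a method, and that method does not connect with the distress management it describes elsewhere. It is also fair that the remedy comes late: recruitment began in late 2024, and a log cannot be applied to sessions already run.

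**Conclusion.** The stated method is weak, though not blind. Followed as written, it would tend to undercount harm during modules, which reaches the count only in retrospect, and it would miss harm in any child without post data. Distress that the psychologists refer or escalate has no stated path into the count.

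On size: with 5 of 28 leaving, the most that still meets 80% completion, no event seen in completers is compatible with 0 to 18% of enrolled children having been harmed. This rests on two assumptions: that the leavers give no post data, and that nothing was missed in completers. If leavers are offered and return the post form, that range narrows. If harm in completers is also missed, its upper end rises. The 80% is a feasibility threshold, not a cap, so more than 5 could leave. The figures describe what the method could fail to see; they are not evidence that harm has occurred.

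This should be changed, since events not recorded at the time may not be recoverable at analysis.

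**What to change.** Amend the adverse event sentence in Data Management as follows:

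- From the amendment onward, adverse events also include distress events, referrals and escalations logged at each module by the delivering psychologists, in addition to those found by pre-post review.
- Children who stop early are offered the post form, including the acceptability and open-ended items, and may give a reason if they wish. This keeps the right to withdraw without one.
- Harms are reported with all enrolled children as denominator, stating how many lack post data and which modules were delivered before logging began.

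This changes what is recorded and reported, not how distress is managed. The cost is a brief log entry per module by staff already present, one form offered to leavers, and an amendment reported to the ethics committee and the registry. Modules already delivered stay uncovered, and the report should say so. If a fuller safety procedure already does this, a sentence pointing to it and naming the denominator is enough.
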